## Abstract

**Background:**

We have recently completed an evaluation of the safety and feasibility of intravenous delivery of autologous bone marrow in patients with progressive multiple sclerosis (MS). The possibility of repair was suggested by improvement in the neurophysiological secondary outcome measure seen in all participants. The current study will examine the efficacy of intravenous delivery of autologous marrow in progressive MS. Laboratory studies performed in parallel with the clinical trial will further investigate the biology of bone marrow-derived stem cell infusion in MS, including mechanisms underlying repair.

**Methods/design:**

A prospective, randomised, double-blind, placebo-controlled, stepped wedge design will be employed at a single centre (Bristol, UK). Eighty patients with progressive MS will be recruited; 60 will have secondary progressive disease (SPMS) but a subset (*n* = 20) will have primary progressive disease (PPMS). Participants will be randomised to either early or late (1 year) intravenous infusion of autologous, unfractionated bone marrow. The placebo intervention is infusion of autologous blood. The primary outcome measure is global evoked potential derived from multimodal evoked potentials. Secondary outcome measures include adverse event reporting, clinical (EDSS and MSFC) and self-assessment (MSIS-29) rating scales, optical coherence tomography (OCT) as well as brain and spine MRI. Participants will be followed up for a further year following the final intervention. Outcomes will be analysed on an intention-to-treat basis.

**Discussion:**

Assessment of bone marrow-derived Cellular Therapy in progressive Multiple Sclerosis (ACTiMuS) is the first randomised, placebo-controlled trial of non-myeloablative autologous bone marrow-derived stem cell therapy in MS. It will determine whether bone marrow cell therapy can, as was suggested by the phase I safety study, improve conduction in multiple central nervous system pathways affected in progressive MS. Furthermore, laboratory studies performed in parallel with the clinical trial will inform our understanding of the cellular pharmacodynamics of bone marrow infusion in MS patients and the mechanisms underlying cell therapy.

**Trial Registration:**

ISRCTN27232902 Registration date 11/09/2012. NCT01815632 Registration date 19/03/2013

## Background

Multiple sclerosis (MS) affects approximately 2.5 million people worldwide. Although most patients present with relapsing-remitting disease, over 80 % of patients develop progressive disability. Although treatments to reduce relapse frequency are available, very limited progress has been made in the prevention or reversal of progressive disability. The development of cell therapy to treat progressive MS is an attractive option due to the multiplicity of actions that may be employed including immunomodulatory, neuroprotective and reparative processes.

We have recently completed a phase I safety and feasibility study of intravenous autologous bone marrow (BM) infusion in patients with progressive MS [1]. This study not only confirmed safety but also raised the possibility of partial repair; conduction times in multiple central nervous system (CNS) pathways collated as a composite score known as the global evoked potential (GEP) [2, 3] improved in all patients studied (*n* = 6) [1]. We believe that this requires urgent investigation to determine if autologous bone marrow infusion does indeed exert a genuine reparative effect in progressive MS.

## Methods

### Objective and hypothesis

We hypothesise that intravenously delivered autologous bone marrow cell therapy (BMCT) in chronic MS offers significant benefit. We further postulate that the mechanisms are multiple, and include immunomodulation *and* reparative and/or neuroprotective effects within the CNS; and are offered by one or more BM stem cell sub-populations, jointly contributing to the therapeutic impact. Exploring and understanding these mechanisms, and the biology of the cells responsible, will allow the development of more effective reparative cell therapy in MS.

On this underlying hypothesis, we propose a phase II controlled trial in parallel with a significant body of translational and back-translational laboratory research, with the following objectives:To determine the efficacy of intravenous infusion of autologous bone marrow cells in patients with progressive MSTo collect additional safety data regarding the collection and intravenous infusion of bone marrow cells in those with MSThe laboratory arm of the study will explore the mechanisms underlying the efficacy of infusion of bone marrow cells in MS to determine how these can be augmented and, potentially, how the need for bone marrow harvest can be obviated.

### Trial design

Assessment of bone marrow-derived Cellular Therapy in progressive Multiple Sclerosis (ACTiMuS) is a double blind, randomised, placebo-controlled single centre, stepped wedge design trial [4] in adults with progressive MS and Expanded Disability Status Scale (EDSS) score 4.0–6.0 (walking affected by disease, but still able to walk, with aids if necessary; distance as determined by the Ambulation Score). The study schema is presented in Fig. 1.

**Fig. 1 Fig1:**
[figure not shown]
Study schema for the ACTiMuS trial

### Sample size estimation

We will randomly allocate 40 patients, 30 with secondary progressive disease (SPMS) and 10 with primary progressive disease (PPMS), to each arm of the study, allowing a difference of between 0.63 and 0.73 of a standardised difference in GEP between the arms to be detected with 80 % power at the 5 % significance level, assuming a loss to follow-up rate of between 0 and 25 % respectively. Our experience suggests that, given the close involvement of patients and staff, we will achieve around 95 % follow-up.

### Eligibility and enrolment

Participants will be patients attending the Bristol and Avon Multiple Sclerosis (BrAMS) Unit, North Bristol NHS Trust, UK. To enter the study, participants will have progressive MS and will have given informed consent. In addition, they must fulfil the inclusion and exclusion criteria as detailed in Table 1.

**Table 1 Tab1:** Eligibility criteria for the ACTiMuS trial

Inclusion criteria	Exclusion criteria
Either sex, 18–65 years old	Pregnancy, breastfeeding or lactation
Diagnosis of clinically definite MS as defined by the McDonald criteria	History of autologous/allogeneic bone marrow transplantation or peripheral blood stem cell transplant
	Bone marrow insufficiency
MS disease severity EDSS 4–6	History of lymphoproliferative disease or previous total lymphoid irradiation
	Immune deficiency
Disease duration >5 years	History of current or recent (<5 years) malignancy
Disease progression (not attributable to relapse) in the year prior to entry	Chronic or frequent drug-resistant bacterial infections or presence of active infection requiring antimicrobial treatment
Signed, written informed consent	Frequent and/or serious viral infection
Willing and able to comply with study visits according to protocol for the full study period	Systemic or invasive fungal disease within 2 years of entry to study
	Significant renal, hepatic, cardiac or respiratory dysfunction
	Contraindication to anaesthesia
	Bleeding or clotting diathesis
	Current or recent (within preceding 12 months) immunomodulatory therapy other than corticosteroid therapy
	Treatment with corticosteroids within the preceding 3 months
	Significant relapse within preceding 6 months
	Predominantly relapsing-remitting disease over preceding 12 months
	Radiation exposure in the past year other than chest/dental x-rays
	Previous claustrophobia
	The presence of any implanted metal or other contraindication to MRI
	Participation in another experimental study or treatment within previous 24 months

### Randomisation and blinding

Randomisation will be centrally allocated using the infrastructural facilities of the Bristol Randomised Trials Collaboration (Departments of Social and Community Medicine), which provides web-based automatic randomisation services. Randomisation will be stratified by disease type (PPMS versus SPMS) using a permuted block design to ensure balance of allocation to the immediate or delayed treatment groups. Allocations are only released once the new study participant is logged into the system, thus ensuring allocation concealment. The results of randomisation will be held by NHS Blood and Transplant (NHSBT) and will be released only when the trial is to be unblinded and at the request of the Trial Management Committee.

During infusion, the trial product (blood or marrow) will be shielded from the participants using covered giving sets and obscuring the cannula site from the participant. Trial assessors do not have access to information regarding the order in which blood and marrow are infused. The level of unmasking of participants, treating physicians and assessors will be assessed by direct questioning at the end of the study.

### Trial interventions

#### Venesection

Venesection of approximately 500 mL will be performed at entry and at 1 year. Blood donation will be performed in accordance with NHS Blood and Transplant standard operating procedures which comply with UK guidelines [5]. Briefly, a cannula is inserted in the antecubital fossa and venesection is performed with a sphygmomanometer cuff inflated to 60 mmHg.

#### Bone marrow harvest and infusion

Bone marrow harvest will be performed under general anaesthesia. Approximately 500–600 mL marrow will be collected together with bone marrow trephine. The marrow aspirate will be filtered, bagged and labelled by NHSBT. An infusion of either blood or marrow will be performed on the day of bone marrow harvest. Analgaesia will be offered and a check FBC will be performed. Iron replacement therapy will be given if Hb <9.5 g/dL pre-harvest or Hb <7.5 g/dL post-harvest (ferrous sulphate 200 mg od for 1 month). One year later, intravenous infusion of blood or thawed marrow will be performed (whichever was not infused at the time of harvest).

Bone marrow trephines and a small sample of the bone marrow aspirate will be retained for back-translational laboratory research studies running in parallel with the clinical trial if specific written informed consent is given. Blood samples for research purposes may be requested throughout the duration of the study.

### Outcome measures

#### Primary outcome measure

Multimodal evoked potentials will be examined at 0, 6, 12, 18 and 24 months. Evoked potential abnormalities will be quantified according to a 4-point graded ordinal score modified from Leocani et al. (0 = normal; 1 = increased latency; 2 = increased latency and abnormal amplitude; 3 = absent) [3]. The primary outcome measure is change in GEP in the 12-month period after infusion of autologous marrow.

The recording of the evoked potentials shall be in accordance with the Guidelines of the International Federation of Clinical Neurophysiology [6], and analysis will be performed using standard methods [7] (Table 2). Electrophysiological responses shall be considered abnormal if they exceed 2.5 standard deviations of the normal values or cannot be detected.

**Table 2 Tab2:** Method for recording of multimodal evoked potentials

Visual evoked potentials (VEPs) will be evoked with a rear-projected checkerboard pattern using an opto-mechanical device subtending 30 degrees at the retina, check-size 1 degree, white brightness of 150cdm^−2^ and contrast 87.5 %.
Monaural stimulation will be delivered via earphones to each side with rarefaction click stimuli of 0.1 ms duration at an intensity of 75 dB above the subjective hearing threshold whilst the contralateral ear is masked with white noise.
Sensory evoked potentials (SEPs) will be obtained by delivering electrical stimulation with square wave pulses of 0.2 ms duration to the median and the posterior tibial nerves, at the wrist and ankle respectively.
Motor evoked potentials (MEPs) will be recorded from electrodes situated over the abductor pollicis brevis muscle in the hand and the abductor hallucis in the foot using a 9 cm circular coil held over the vertex. The central motor conduction time (CMCT) will be calculated by subtracting ½(M + F + 1) from the MEP latency where M is the distal motor latency and F is the minimum F wave latency.
The GEP score will then be calculated as the sum of left and right brainstem auditory evoked potential (BSAEP) and VEP scores (0–12) and left and right upper and lower SEPs (0–12) and CMCTs (0–12).

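### The CMCT formula in Table 2 has the wrong sign on its 1 ms term: as printed every CMCT is 1 ms too short, and grades change only if the normal limits rest on a different formula

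*Protocol article*

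**What the plan says.** All of this stands in the Protocol article under Primary outcome measure, including Table 2.

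- Formula: the CMCT is found by "subtracting ½(M + F + 1) from the MEP latency where M is the distal motor latency". The symbol F stands for the shortest F wave latency. The formula appears once. The article does not explain the 1 and corrects the formula nowhere else.
- Abnormality: a response is "considered abnormal if they exceed 2.5 standard deviations of the normal values or cannot be detected". The article gives neither the normal values nor the formula behind them.
- Grading of each response: "0 = normal; 1 = increased latency; 2 = increased latency and abnormal amplitude; 3 = absent".
- Weight: four limb CMCTs contribute 0 to 12. The SEPs contribute another 0 to 12, and the visual and auditory responses together the remaining 0 to 12.
- Use: "The primary outcome measure is change in GEP in the 12-month period after infusion of autologous marrow".

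The same section refers to cited standard methods for the analysis of the recordings. That source is not available here.

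**The concern.** CMCT is what remains of the MEP latency once the cord-to-muscle time is removed, so the subtracted term has to equal that peripheral time. An F wave travels from the stimulation site up to the cord, turns round at the motor neurone and returns to the muscle, so its latency includes the turnaround. Recovering the one-way peripheral time from F and M means subtracting the turnaround. Table 2 adds 1 instead.

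The formula feeds one third of the only primary outcome. Because CMCT enters that outcome through a cut at 2.5 SD, a constant error in the latency can change a grade. Whether it does depends on how the normal limits were obtained.

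**Working it through.** **Inputs.** From Table 2: the subtracted term ½(M + F + 1), M the distal motor latency, F the minimum F wave latency. From the text above Table 2: the 2.5 SD limit and grades 0 to 3. Assumed: the 1 is a turnaround of 1 ms; the normal SD of CMCT is 0.7 to 2.0 ms. Neither assumption is in the article.

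**Score range, as stated.** Four limbs × 3 = 12 points for CMCT; three blocks of 12 give 36; CMCT share 12/36 = one third. This agrees with Table 2.

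**Peripheral time.** Let P be the conduction time between stimulation site and cord, and t the turnaround.

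- F = P + t + P + M = 2P + t + M
- Peripheral time = P + M = ½(M + F − t)
- Printed term minus peripheral time = ½(M + F + 1) − ½(M + F − t) = ½(1 + t)

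The printed CMCT is therefore short by ½(1 + t): 0.5 ms at t = 0, 0.75 ms at t = 0.5 and 1.0 ms at t = 1. No non-negative turnaround makes the plus sign right. Against the minus-1 formula the difference is always ½(M + F + 1) − ½(M + F − 1) = 1 ms, whatever M and F are.

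**Illustrative latencies (assumed, t = 1 ms).**

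| Limb | P | M | F | True CMCT | MEP latency | Printed formula | Minus-1 formula |
|---|---|---|---|---|---|---|---|
| Upper | 10 | 3.5 | 24.5 | 7.0 | 20.5 | 20.5 − 14.5 = 6.0 | 20.5 − 13.5 = 7.0 |
| Lower | 20 | 5.0 | 46.0 | 15.0 | 40.0 | 40.0 − 26.0 = 14.0 | 40.0 − 25.0 = 15.0 |

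**Effect on grades.** Take the limit as L = normal mean + 2.5 SD.

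- *Limits from the minus-1 formula, or from an outside source without the error.* With t = 1, a limb is called prolonged only when its true CMCT exceeds L + 1 ms. In SD units the cut becomes 2.5 + 1/SD: 3.93 for SD 0.7 ms, 3.50 for 1.0, 3.17 for 1.5, 3.00 for 2.0. Limbs between L and L + 1 ms count as normal latency.
- *Limits from the printed formula.* The patient's value and the limit are both 1 ms low, the shift cancels and no grade changes. Only the reported CMCTs are wrong.

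**Does a higher cut reduce responsiveness to change?** That depends on how many limbs lie near the cut, not on how many lie above it. Suppose patients' CMCT z-scores are normal with mean 3 to 4 and SD 2.5 to 3 (assumed). The density at the shifted cut, relative to that at 2.5, is then 0.95 to 1.20. At the two ends, both with z-score SD 2.5 and the cut at 3.93:

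- mean 3: exp(−½(0.93/2.5)²) / exp(−½(0.5/2.5)²) = 0.933/0.980 = 0.95
- mean 4: exp(−½(0.07/2.5)²) / exp(−½(1.5/2.5)²) = 1.000/0.835 = 1.20

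Under these assumptions responsiveness is about unchanged or slightly higher.

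**The case against.** The best defence is that this is a slip in print. The formula occurs once, in a table of a condensed article whose text says the analysis follows standard methods, and nothing shows that any latency was processed with plus 1. That stands as a reason to check the laboratory's formula before recomputing anything. It does not clear the text, which gives an explicit and wrong formula for a component of the primary outcome.

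A second defence also stands: a laboratory that used one formula for both patients and normal values would have no limb mis-graded.

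A reader might infer three stronger things, none of which the article supports.

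- *The trial result is biased.* The same formula applies in both arms and at every visit, and the Trial analyses section compares randomised arms with adjustment for baseline GEP. The offset does not by itself favour either arm.
- *The GEP becomes less able to show a treatment effect.* Moving the cut changes the level of the score. The density check shows no clear loss of responsiveness under plausible assumed distributions.
- *Comparability with earlier GEP data is lost.* The score is already described as modified from an earlier one, no comparison with historical values is planned under Trial analyses, and the formula behind earlier data cannot be seen.

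Absent responses score 3 whatever the formula, which further limits how many limbs could be affected.

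**Conclusion.** The point holds as a formula error. The plus sign is wrong for any non-negative turnaround. Every CMCT computed as printed is 1 ms too short if the turnaround is 1 ms, and 0.5 to 1 ms too short over a range of 0 to 1 ms. This follows from the article's own definitions of M and F and the path of the F wave.

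The effect on the primary score is conditional. If the normal limits came from the minus-1 formula or from elsewhere, the effective abnormality limit for CMCT, in one third of the GEP, moves from 2.5 SD to about 3.0 to 3.9 SD, for an assumed normal SD of 2.0 down to 0.7 ms. If the limits came from the printed formula, the grades stand. The article does not say which case applies, so mis-grading is possible but not shown. Neither bias between arms nor a loss of sensitivity is shown.

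**What to change.** 1. Correct the subtracted term in Table 2 to ½(M + F − 1) and state what the 1 represents.
2. Confirm with the neurophysiology laboratory which formula it actually used, and that the normal limits were derived with the same one. Record both in the protocol or the analysis plan.
3. Only if plus 1 was applied, recompute the CMCTs and their grades from the stored MEP, M and F latencies, blind to arm and before unblinding. Any later rescoring would look data-driven.

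The cost is a one-character correction and one query to the laboratory, plus at most a recalculation from stored latencies. No new recordings and no change to design or sample size are needed. Recruitment was still under way when the article appeared (Trial status).

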#### Secondary outcome measures

Adverse events (AEs), serious adverse events (SAEs), safety tests, clinical measures of disability, optical coherence topography (OCT) and magnetic resonance imaging (MRI) findings are included as secondary outcome measures.

#### Adverse events

Any unfavourable and unintended sign, symptom or illness that develops or worsens during the period of the study is classified as an AE, whether or not it is considered to be related to study interventions. Adverse events include unwanted side effects, toxicity or sensitivity reactions, abnormal laboratory results and injury or intercurrent illnesses, and may be expected or unexpected.

Furthermore, if an adverse event:results in deathis life threateningrequires hospitalisation or prolongation of existing hospitalisationresults in persistent or significant disability or incapacityconsists of a congenital anomaly or birth defector is considered by the investigator to be an important medical event,

then it is classified as an SAE and must be reported to the trial coordinating centre as soon as possible.

It is expected that some participants will be hospitalised during the study for MS-related problems. These events should be classified as SAEs and reported accordingly. However, a hospital admission for a procedure planned before entry into the study will not be recorded as an SAE.

Expected adverse events include:Local bruising and discomfort following bone marrow harvestIncrease in lower limb spasticity following bone marrow harvestAcute urinary retention following bone marrow harvestTemporary exacerbation of MS following general anaesthesiaHypovolaemia or anaemia following blood and marrow donationHypersensitivity to marrow cryopreservativeExacerbation of MS due to sepsis, for example, urinary tract infection or chest infectionAssessment at or admission to hospital following fall

#### Clinical laboratory tests for safety analyses

Blood taken for safety analyses will be screened as follows: urea and electrolytes, liver function tests, full blood count with differential white cell count, coagulation, group and save, C-reactive protein, glucose, calcium, magnesium, chloride, bicarbonate, phosphate, viral serology (including cytomegalovirus, Epstein-Barr virus, herpes simplex virus, varicella zoster virus, toxoplasmosis, hepatitis B and C, human immunodeficiency virus, human T cell lymphoma virus and syphilis screening. Urinalysis (microscopy and culture) will also be performed.

#### Clinical outcome measures

Clinical outcomes will be assessed at entry and after each intervention at 6 weeks, 6 months and 1 year. The clinical rating scales will include the widely used Expanded Disability Status Scale (EDSS) [8] together with the Multiple Sclerosis Functional Composite (MSFC). The latter is a three-part quantitative assessment including a timed walk, nine-hole peg test and Paced Auditory Serial Addition Test (PASAT) [9]. In addition, participants will be asked to complete the MS Impact Scale (MSIS-29), which is a well-validated patient-completed rating scale [10–13].

#### Paraclinical outcome measures

##### Magnetic resonance imaging (MRI)

Participants will undergo cranial and spinal MRI at three time points: at baseline and at the end of years 1 and 2. The secondary MRI outcome measures will relate to 1) lesion load, 2) atrophy measures both of the brain and of cross-sectional area of the spinal cord [14], and (3) changes in mean diffusivity [15].

Exploratory analysis of the resting-state fMRI data will investigate correlations between network patterns and ‘strength’ of networks connectivity from the resting-state fMRI with classifications revealed by the various evoked potential studies [16–18].

##### Optical coherence tomography (OCT)

Measurement of retinal nerve fibre layer thickness [19] and macular volume [20] using OCT is increasingly recognized as an objective outcome measure which accurately reflects axonal loss.

The measures taken for secondary outcomes are as follows:Safety: evaluation of number and nature of adverse eventsPhysician-based EDSS: time to EDSS progression of at least one point from a baseline EDSS of 4.0, 4.5 or 5.0 or at least 0.5 point from a baseline EDSS ≥5.5.Patient-based MSIS-29 physical impact scale version 2: overall mean change from baseline to end of studyMSFC: overall mean change of z-scores, from baseline to final visitMRI head: T1 weighted 3D gradient echo, 3D FLAIR, DTI and MRI cord (3D gradient echo)OCT: macular volume, thickness of retinal cell layerAnnual overall patient and treating physician assessments of efficacy.

